## Design

An international multicenter randomized clinical trial will be performed. Centers in the Netherlands (table 1), Belgium, Denmark, France, Germany, Italy, Latvia, Portugal, Spain, Sweden, Switzerland, United Kingdom, USA and Canada will participate (table 2 and figure 1 and 2). The multicenter design is necessary to recruit all patients in the inclusion period of 2 years. Early surgery will be compared with prolonged conservative treatment. The selection and randomization procedure is depicted in figure 3. The overall range for randomization of the AAS is an AADI between 5–12 mm. Participating centers/countries are allowed to randomize different intervals of subluxation. The intervals are predefined as 5–8 mm, 5–12 mm and 8–12 mm. Demographic and clinical data will be collected of each patient. The randomization of all patients will be performed centrally at the LUMC by the trial coordinator and datamanager by a concealed randomization list in random permuted blocks.

After a follow up of 5 years the main research question will be answered, although the total follow-up will be 10 years. Patients excluded from the trial will be followed in a cohort group and treated according to the usual care by surgical fixation or conservative treatment. The LUMC will function as the research and data coordinating center, where the data will be collected, analyzed and publications prepared. Eligibility criteria will differ from site to site, according to local perceptions of equipoise. These efforts will increase the generalization of the results. The authors have full access to the data, direct the data-analysis and are responsible for decisions regarding publication. The principal investigator and the trial coordinator assume full responsibility for the integrity and interpretation of the data.

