### Sample size/power calculation

The sample size is calculated on the basis of the outcome difference during the follow-up period of at least 5 years. Hypothetically, 8% of included patients will worsen in the 5 year follow up period resulting in an event (Kaplan Meier) (16,21). In the early surgery group the event rate is expected to be 2% or less [44]. 2% is chosen because it has to be a save alternative to 'wait and see'. A two-sided log rank test with an overall sample size of 250 patients, achieves 90% power at a 0.05 significance level to detect a difference in groups 1 and 2 after 5 years of follow up. Patients enter the study during an accrual period of 2 years. 50% of the enrolment is complete when 50% of the accrual time has past. A follow-up period of 5 years with a 20% loss from group 1 and a 20% loss from group 2 is calculated.

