### Primary and secondary outcome parameters

***The primary outcome ***is the occurrence of an event. Events are defined as 1) neurological deficit, 2) radiological progression, 3) surgery, 4) resurgery, 5) death. (see table 5).

1). Neurological deficit is defined as a worsening in the Ranawat scale to IIIA or IIIB, or a deterioration of the MDI score >3 points. The Ranawat classification is a neurological classification and useful in evaluating patients, planning treatment and evaluating results. Class I patients have no neurological deficit, Class II patients have subjective weakness with hyperreflexia and dysesthesia. Class IIIA patients have objective weakness and long tract signs. Class IIIB patients are wheelchair bound or bedridden. The Ranawat classification fails to differentiate reliably between classes II and IIIA, the area of most clinical interest to the operating surgeon [45]. Casey and Crockard developed and validated the MDI according to the Stanford HAQ. The MDI consists of 10 functional questions. The more severe a patient has been disabled the higher the score [45].

2). Radiological progression is defined as an enlarged AADI of more than 12 mm, development of VT with impingement of the spinal cord or medulla oblongata, or signs of myelopathy. The Redlund Johnell method will be used to measure the severity of VT, which is the distance of the base of C2 to the palato-occipital line of McGregor (less than 34 mm in men and 29 mm in women) [11].

3). Incidence of surgery in the conservative treatment group. One of the goals of the conservative treatment is to avoid surgery for intolerable pain for example. The surgical rate is therefore an indication of the success or failure of the conservative treatment policy.

4). The incidence of resurgery at the cervical spine in the early surgery group will be an indication of the failure rate for surgery.

5). Death: all causes.

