### Statistical analysis

The researchers will be aware of allocation to early surgery or conservative treatment at the time of the statistical analyses. There will be an intermediate analysis after 2 years of follow up. The intermediate outcome measures are progression of AAS and VT with or without (pain) complaints and neurological disability (measured with the MDI and Ranawat). The main analyses will be performed after 5 years and 10 years of follow up. At these intervals the primary outcome parameter is the occurrence of an event as described in table 5. Baseline comparability will be investigated by descriptive statistics to examine if randomization was successful. Differences in success rates between both groups are calculated, together with 95 percent confidence intervals. In addition to an analysis of the difference in outcome between the two groups analyses of the difference in time to progression will be carried out. Continuous outcomes are evaluated as change scores (differences between baseline measurement and each follow-up measurement). Multivariable analyses are performed to adjust for the eventual differences between the groups at baseline in prognostic indicators. All the analyses are performed according to the intention-to-treat principle. An additional per protocol analysis will be performed comparing patients in the conservative group who received surgery with patients in the same group who had not and with patients in the surgery group. To compare the actual treatment sec instead of strategies an explorative analysis will be performed in subgroups of all patients who actually received surgery and who did not receive surgery in both groups. All patients withdrawn from the study are included in the analysis until the time of withdrawal.

To answer the third research question, explorative analyses are conducted to investigate whether the treatment effect varies in specific subgroups of patients. Using logistic regression for success rate and linear regression for severity of the disability, each prognostic indicator is checked for interaction with treatment.

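### Adjustment covariates are picked from observed baseline imbalance by analysts who know allocation; a short set led by baseline AADI should be named in advance

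*Protocol article*

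**What the plan says.** **Covariate rule.** Protocol article, Statistical analysis: "Multivariable analyses are performed to adjust for the eventual differences between the groups at baseline in prognostic indicators". The step before it is a descriptive comparison of the arms at baseline, made to judge whether randomization worked. The same section says that the researchers will know the allocation when they analyse. It names no prognostic indicator.

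**Enrolment windows.** Design: "Participating centers/countries are allowed to randomize different intervals of subluxation". The permitted windows are 5–8, 5–12 and 8–12 mm, and eligibility may vary by site. Allocation is central, "by a concealed randomization list in random permuted blocks". No stratification factor is mentioned, and none is ruled out.

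**Endpoint.** Primary and secondary outcome parameters: "Radiological progression is defined as an enlarged AADI of more than 12 mm", with further criteria for vertical translocation and myelopathy. Radiological progression is one of five event types. Surgery in the conservative arm is another, and the Conservative treatment section lists progressive radiological abnormality among the indications for that surgery.

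**Planned size.** Sample size/power calculation: "Hypothetically, 8% of included patients will worsen in the 5 year follow up period resulting in an event"; "In the early surgery group the event rate is expected to be 2% or less"; "A two-sided log rank test with an overall sample size of 250 patients, achieves 90% power at a 0.05 significance level".

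**The concern.** A covariate earns its place by predicting the outcome. Whether it happens to differ between arms is a different matter. A rule triggered by imbalance can admit a variable that has no bearing on the event and omit one that has a strong bearing but looks balanced. It also leaves the model open until the data have been seen by people who know who received what, so several adjusted results could be produced and one preferred.

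Two features of this trial sharpen the point. Few events are expected, so a list of indicators gathered by imbalance would overload the model. And one baseline variable is tied to the endpoint by definition: the distance left to the 12 mm threshold differs widely across eligible patients, and the enrolment windows link that distance to site. At stake are the credibility and precision of the adjusted estimate, and the reading of any AADI subgroup finding under the third research question.

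**Working it through.** **1. The plan's own figure.** Inputs from Sample size/power calculation: 8% v 2% at 5 years, 250 patients, two-sided 0.05, 90% power. The hazard ratio is ln(0.98)/ln(0.92) = 0.242. For 90% power this needs 21 events (Schoenfeld) or 29 (Freedman). At an average event rate of 5% that is 21/0.05 = 420 or 29/0.05 = 580 patients before loss. With 250 patients the power is 71% or 58%. The stated 90% is not reproduced. That is a separate matter, and this point does not depend on it.

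**2. Events available.** Assuming 1:1 allocation (the ratio is not stated): 0.08 × 125 + 0.02 × 125 = 10 + 2.5 = 12.5 before loss. Treatment plus one covariate leaves 12.5/2 ≈ 6 events per parameter; treatment plus two leaves 12.5/3 ≈ 4.

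**3. Link of AADI to the endpoint.** Distance to the threshold is 12 − 5 = 7 mm at the lower limit, 12 − 8 = 4 mm at the middle cut and almost nothing at the upper limit. A site enrolling 5–8 mm has patients 4 to 7 mm away; a site enrolling 8–12 mm has patients 0 to 4 mm away. AADI can act directly through radiological progression and indirectly through surgery in the conservative arm, so on two of the five event types.

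**4. Chance imbalance without stratification.** The SD of the between-arm difference in the share with high AADI is √(p(1−p) × 2/125). The share p is not given.
- p = 0.3: SD 5.8 points; chance of a difference of 10 points or more 8%.
- p = 0.5: SD 6.3 points; chance 11%.

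**5. Effect on the arm difference.** Assume half the patients are above 8 mm, with conservative-arm risks of 14% above and 2% below (average 8%). Keeping the same 7:1 ratio, the surgery-arm risks are 3.5% and 0.5% (average 2%). An imbalance at the edge of the 95% range is 1.96 × 6.3 ≈ 12.4 points, or 6.2 points either way in each arm. The shift is 0.062 × 12 + 0.062 × 3 = 0.93 points, about 15% of the planned 6-point difference. One SD of imbalance gives about 0.5 points. The sampling SE of the arm difference is √(0.08 × 0.92/125 + 0.02 × 0.98/125) ≈ 2.7 points.

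**6. Simulation.** 2,000 trials per setting, N = 250, 8% v 2%, baseline AADI uniform on 5–12 mm, binary outcome, Firth logistic regression. The triggered rule adjusts for AADI only if the baseline difference has p < 0.10; that threshold is assumed, since the plan gives none.

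| Assumed OR per SD of AADI | Power: unadjusted | AADI prespecified | AADI if imbalanced |
|---|---|---|---|
| 1 | 49.6% | 51.6% | 49.9% |
| 2 | 50.2% | 52.1% | 50.0% |
| 3 | 49.9% | 54.2% | 50.9% |

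Type I error was between 2.8% and 4.2% throughout. The Monte Carlo SE of each power figure is √(0.25/2000) ≈ 1.1 points. The gain over no adjustment is 2 to 4 points. About 2 points appear even at OR 1, where AADI predicts nothing, so not all of the gain can be credited to AADI. The simulation tested one candidate covariate. It did not test free choice among many.

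**The case against.** The strongest reply is that the main comparison does not rest on this sentence. The trial is sized on a log-rank test, and the difference in success rates and the time-to-progression comparison are not described as adjusted; the multivariable analysis reads as a further step. That stands, and it limits the point to the adjusted analysis. It is also fair that the measured benefit is small and that type I error was controlled in the simulation.

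The reply that covariates belong in an analysis plan does not dispose of the matter. The article does not merely leave the list open; it states how the list will be chosen, and that method is poor.

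Several stronger readings are tempting but unsupported:
- *Allocation ignores AADI.* The Design section is silent on strata. A condensed article may omit them, and silence does not show an unstratified list.
- *The analysis ignores AADI.* It may enter as a prognostic indicator, and each indicator is to be checked for interaction with treatment.
- *AADI drives the event.* No AADI–event association is given. Signs and symptoms says that complaints do not track radiological severity, and Background notes that AADI can fall as vertical translocation develops.
- *Balanced variables will be dropped on a significance test.* The plan mentions only descriptive comparison.
- *The result is biased.* Randomization balances AADI in expectation, whatever windows sites use.
- *Imbalance could move the result by 1.5 points, a quarter of the planned effect.* That figure (0.124 × 12) applies the conservative-arm risk gradient to both arms. With the surgery arm's lower planned risk it is about 0.9 points.

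**Conclusion.** The point holds in limited form. The plan fixes a data-dependent rule for choosing covariates, to be applied by analysts who know allocation, in a trial expecting about 12 to 13 events before loss. Baseline AADI is plausibly prognostic because of how the endpoint is built, is linked to site through the enrolment windows, and should be named in advance.

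The size is modest: roughly 2 to 4 power points over no adjustment under assumed odds ratios of 1 to 3 per SD, and a shift of about 0.9 points from an imbalance at the edge of the 95% range under the assumed 7:1 risk gradient. The larger benefit is that the adjusted model is no longer chosen after the data are seen. These figures rest on 1:1 allocation, the plan's own event rates, and AADI distributions and associations that the document does not give.

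**What to change.** - Remove observed baseline difference as the criterion for adjustment.
- Prespecify baseline AADI, either continuous or as 5–8 v >8–12 mm, as the covariate of the adjusted Cox model or the single stratification factor of the adjusted log-rank test. Allow at most one further named factor, and no selection by imbalance. Baseline tables stay descriptive.
- Check the central list. If it is stratified by AADI band or enrolment window, analyse by that factor.
- Allow for enrolment window or site when interpreting the exploratory AADI-by-treatment interaction, since an apparent AADI effect may partly be a site effect.
- Do not stratify the analysis by country as well. Fourteen countries and two bands make 14 × 2 = 28 strata, about 250/28 ≈ 9 patients and 12.5/28 ≈ 0.45 events each, which is too sparse.

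The cost is one changed sentence and one degree of freedom. AADI is already measured for eligibility, so no new data are needed.

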#### Conservative treatment

Conservative treatment consists of antirheumatoid drugs (i.e, NSAID, DMARD, biologicals). The choice of drugs is to the discretion of the rheumatologist. Occurrence of progressive neurological deficits, progressive radiological abnormalities, and intolerable pain represent a failure of conservative management and are an indication for surgical fixation.

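### The per-protocol contrasts are predetermined on the primary event because surgery in the conservative arm is itself an event; the pooled as-treated contrast is biased, though not fixed

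*Protocol article*

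**What the plan says.** Three parts of the protocol article bear on this.

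- **Primary and secondary outcome parameters.** The primary outcome is a composite: "Events are defined as 1) neurological deficit, 2) radiological progression, 3) surgery, 4) resurgery, 5) death". Component 3 is explained as "Incidence of surgery in the conservative treatment group", with the comment "The surgical rate is therefore an indication of the success or failure of the conservative treatment policy". The early surgery arm is treated differently. Its allocated operation is not an event and only a repeat operation counts: "The incidence of resurgery at the cervical spine in the early surgery group will be an indication of the failure rate for surgery".
- **Conservative treatment.** Progressive neurological deficit, progressive radiological abnormality and intolerable pain "represent a failure of conservative management and are an indication for surgical fixation".
- **Statistical analysis.** The main analyses are by intention to treat, with the composite event as primary outcome at 5 and 10 years. Two further analyses are then announced. One, called per protocol and additional, is described as "comparing patients in the conservative group who received surgery with patients in the same group who had not", and the same sentence adds a comparison with the surgery arm. The other, called explorative and meant to compare treatments rather than strategies, uses "subgroups of all patients who actually received surgery and who did not receive surgery in both groups". No outcome is named for either, and nothing says that the surgery component is removed.

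**The concern.** The comparison groups are formed by whether a conservative patient was operated on, and that operation is one of the ways to have the primary event. On the composite, group membership and outcome are then partly the same variable. The groups also arise after randomisation and through failure of the allocated treatment, so they differ in prognosis for reasons unrelated to any effect of surgery.

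At stake is how the supporting analyses would be read. A reader is likely to take a per-protocol analysis as a check on the intention-to-treat result, and the pooled analysis is offered as the effect of the treatment actually received. If operated patients look worse only because their operation was counted as the event, the supporting analyses could appear to contradict a genuine benefit of early surgery.

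**Working it through.** The plan gives no figure for these analyses, so there is none to reproduce. Its planning rates are used only to show size.

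**Inputs**
- Total 250 patients, 8% events in the conservative arm and 2% (or less) in the early surgery arm over 5 years (Sample size/power calculation).
- Assumed: 1:1 allocation, hence 125 per arm, since no ratio is stated; all early-surgery patients receive their operation; no allowance for loss to follow-up.
- Expected events: 0.08 × 125 = 10 conservative; 0.02 × 125 = 2.5 early surgery.
- k = number of conservative patients operated on. The protocol does not give it, so a range is shown. Every one of the k is an event by component 3, so the k lie within the 10.

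**Step 1: operated vs non-operated within the conservative arm**

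Operated: k/k = 100% for every k. Non-operated: (10 − k)/(125 − k).

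| k | Operated | Not operated | Fisher p |
|---|---|---|---|
| 2 | 100% | 8/123 = 6.5% | 0.006 |
| 5 | 100% | 5/120 = 4.2% | 1 × 10⁻⁶ |
| 10 | 100% | 0/115 = 0% | 6 × 10⁻¹⁵ |

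The direction follows from the definition. The size does not, because non-operated patients can still have a neurological, radiological or death event.

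**Step 2: operated conservative patients vs the surgery arm**

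The first group is again at 100%. With the surgery arm rounded to 3/125 = 2.4%, two operated patients already give Fisher p = 0.001.

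**Step 3: pooled operated vs non-operated**

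Operated: (2.5 + k)/(125 + k). Non-operated: (10 − k)/(125 − k).

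| k | Operated | Not operated |
|---|---|---|
| 2.5 | 5/127.5 = 3.9% | 7.5/122.5 = 6.1% |
| 4 | 6.5/129 = 5.04% | 6/121 = 4.96% |
| 5 | 7.5/130 = 5.8% | 5/120 = 4.2% |
| 10 | 12.5/135 = 9.3% | 0/115 = 0% |

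Setting the two rates equal: (2.5 + k)(125 − k) = (10 − k)(125 + k). This reduces to 237.5k = 937.5, so k ≈ 3.9. Below that the planned direction survives in weakened form; above it the sign reverses. In the same data the randomised comparison stays at 2% vs 8% throughout.

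**Step 4: the label**

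The conservative strategy itself provides for surgery once conservative management has failed. A patient operated on for that reason has followed the protocol. Splitting the arm by that operation does not separate adherers from deviators.

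**The case against.** Four points can be made for the plan.

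1. **No outcome is named.** The same paragraph covers continuous change scores, and pain, EuroQol and SF-36 are listed as secondary outcomes. On those, or on the MDI score itself, the 100% rate does not arise. This stands as a limit on the claim. However, the composite is the stated primary outcome at 5 and 10 years and nothing exempts these analyses from it. On the other outcomes the contrasts remain confounded by indication, because failure is the route to surgery.
2. **The detail may be in an analysis plan not shown.** That could settle the outcome, but the comparison groups are already stated here, and it is the groups that are badly chosen.
3. **These analyses are secondary.** True. One is called additional, the other explorative, and the main analyses are by intention to treat. This limits the severity.
4. **The pooled analysis need not mislead.** This also stands in part: at k = 2.5 it keeps the planned direction.

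A reader might go further and infer that the pooled result is fixed by definition too, or that it must contradict the intention-to-treat result. The documents do not support either: the allocated operation in the early surgery arm is not an event, k is unknown, and the sign depends on it.

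A reader might also infer immortal-time bias, on the ground that operated conservative patients had to be event-free until surgery. They did not. Neurological deficit and radiological progression are events in their own right, and progression of either kind is an indication for surgery, so some patients may have had an event before the operation. They had only to be alive and in follow-up.

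**Conclusion.** The concern holds in a limited form. On the composite event, both per-protocol contrasts have a 100% rate on one side and their direction carries no information about surgery. The per-protocol label is wrong. The pooled contrast is biased against surgery, because each operated conservative patient enters the operated group as a guaranteed event. Whether that reverses the sign depends on whether more or fewer than about 4 of the 10 expected conservative events involve surgery.

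These figures rest on equal arms, full uptake of surgery in the early surgery arm, no loss to follow-up, and the 8% and 2% planning rates. The 100% rate rests on none of them; it needs only the event definition in the text (Table 5 was not available to check) and use of the composite as outcome.

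Severity is moderate. The randomised intention-to-treat comparison, the sample size and the data collection are not affected by this point.

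**What to change.** - State that none of the three contrasts (operated vs non-operated conservative patients, operated conservative patients vs the surgery arm, pooled operated vs non-operated) will be run on the composite event.
- Drop the per-protocol label.
- If the effect of actual treatment is wanted, define an outcome that excludes surgery and resurgery, for example neurological deficit or death, with radiological progression added if wanted. Fit a time-to-event model with surgery as a time-dependent covariate, adjusted for the AADI, Ranawat, MDI and pain values already collected.
- Label that analysis exploratory. Say that it is imprecise: on the planning rates there are about 10 events in the conservative arm, and an outcome without surgery may have fewer, which supports little adjustment. Say also that confounding by indication may remain.

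One repair to avoid is a per-protocol analysis that censors conservative patients at surgery. Surgery after failure is not a deviation, censoring there would censor an event under component 3, and weights modelled from so few operations would be unstable.

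The cost is a change of wording and modest programming. No new data are needed.

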### Main research questions

Null hypothesis; there is no difference in outcome between early surgical fixation and prolonged conservative treatment in patients with AAS with an AADI between 5 and 12 mm without neurological complaints. Because of the many uncertainties in the rheumatoid arthritis process the following research questions will be answered.

1. Does early surgery in neurological intact patients with RA and radiological signs of AAS result in less progression of C1–C2 subluxation and VT with or without complaints and neurological disability compared to prolonged conservative treatment?

2. Is early surgery more cost-effective than prolonged conservative treatment in this patient population?

During the explorative analyses the next questions will be answered.

3. Is it possible to define subgroups, which benefit most from one of the allocated treatment strategies?

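### For success rate, research question 3 rests on an odds-ratio interaction alone, which is not a test of equal absolute benefit and often has no finite estimate at the planned event counts

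*Protocol article*

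**What the plan says.** Under the main research questions, the protocol article lists a third, explorative question: "Is it possible to define subgroups, which benefit most from one of the allocated treatment strategies". The statistical analysis section repeats that "explorative analyses are conducted to investigate whether the treatment effect varies in specific subgroups of patients" and fixes the method: "Using logistic regression for success rate and linear regression for severity of the disability, each prognostic indicator is checked for interaction with treatment".

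The same section gives the main comparison of the primary outcome on an absolute scale: "Differences in success rates between both groups are calculated, together with 95 percent confidence intervals". It also announces an analysis of time to progression.

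The sample size section supplies the expected counts. For conservative treatment, "8% of included patients will worsen in the 5 year follow up period resulting in an event"; for surgery, "In the early surgery group the event rate is expected to be 2% or less". The total is 250 patients. The article names no absolute-scale subgroup measure for success rate and no method for sparse cells.

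**The concern.** There are two separate difficulties with the logistic half of the method.

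- **Scale.** A treatment-by-indicator term in a logistic model is zero when the odds ratio is the same in each subgroup. If the indicator predicts the event, as a prognostic indicator does, a common odds ratio implies different absolute benefits, and a common absolute benefit implies different odds ratios. The test can be silent when one subgroup gains several times more than another. It can also signal when both gain the same number of points.
- **Sparse events.** The early surgery arm is expected to have two or three events. Splitting them by a two-level indicator often leaves a cell with none, and the maximum-likelihood interaction odds ratio then runs to zero or infinity.

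The stated objective is the best timing of surgery for patients at risk. For that, the number of events prevented at each level of baseline risk matters. A null odds-ratio interaction, reported alone, invites the reading that all patients benefit alike.

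**Working it through.** **Inputs.** From the sample size section: 8% v 2% events over 5 years, 250 patients, 20% loss per arm. Allocation is not stated; 1:1 is assumed (125 per arm, or 100 if the patients lost contribute nothing). Subgroup splits and subgroup risks are assumptions.

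**The plan's own figure.** The article states: "A two-sided log rank test with an overall sample size of 250 patients, achieves 90% power at a 0.05 significance level". The hazard ratio is ln(0.98)/ln(0.92) = 0.242, and expected events are 125 × 0.08 + 125 × 0.02 = 10 + 2.5 = 12.5. Schoenfeld power is Φ(√(12.5/4) × |ln 0.242| − 1.96) = Φ(0.55) = 71%. Over the variants tried (Schoenfeld, Freedman, two proportions, with and without loss) power ran from 49% to 78%, so the 90% is not reproduced. That is a separate matter. Only the event rates are used below.

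**Scale.** The planned odds ratio is (0.02/0.98)/(0.08/0.92) = 0.235. Holding it constant:

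| Control risk | Surgery risk | Absolute benefit |
|---|---|---|
| 4% | 0.97% | 3.0 points |
| 8% | 2.0% | 6.0 points |
| 16% | 4.3% | 11.7 points |

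The logistic interaction is exactly null throughout. Conversely, a constant 6-point benefit gives an odds ratio of 0.235 at 8% v 2%, but (0.06/0.94)/(0.12/0.88) = 0.47 at 12% v 6%.

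**Zero-event cells.** With 125 per arm and a 50/50 indicator (cells of 62 and 63), a surgery cell is empty with probability 0.98^62 = 0.286 or 0.98^63 = 0.280. A conservative cell is empty with probability 0.92^62 = 0.006 or 0.92^63 = 0.005. P(at least one empty) = 1 − 0.714 × 0.720 × 0.994 × 0.995 = 0.49. The same formula gives:

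| Event rates | 125 per arm, 50/50 | 125 per arm, 20/80 | 100 per arm, 50/50 | 100 per arm, 20/80 |
|---|---|---|---|---|
| 8% v 2% | 49% | 70% | 61% | 78% |
| 16% v 4% | 15% | 38% | 24% | 48% |
| 20% v 5% | 8% | 28% | 15% | 38% |
| 30% v 10% | 0.3% | 7% | 1% | 12% |

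**Precision when no cell is empty.** At expected counts with 125 per arm (50/50), the variance of the log ratio of odds ratios is 2 × (1/5 + 1/57.5 + 1/1.25 + 1/61.25) = 2.07. The standard error is 1.44, and the 95% interval spans a factor of exp(1.96 × 1.44) ≈ 17 each way (about 23 with 100 per arm).

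**What the risk-difference scale would give.** The standard error of the difference between two subgroup risk differences is √[2 × (0.08 × 0.92 + 0.02 × 0.98)/62.5] = 5.5 points (6.1 with 50 per cell). The 95% half-width is about 11 to 12 points, against an overall effect of 6 points.

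**How far the tests diverge.** Simulation with 20,000 trials, 125 per arm, 50/50 split, odds ratio constant at 0.235, two-sided 0.05. The corrected test adds one event and one non-event per cell.

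| Control risks in the two subgroups | Logistic likelihood-ratio test rejects | Risk-difference test rejects (corrected) |
|---|---|---|
| 14% and 2% | 4% | 40% (27%) |
| 12% and 4% | 5% | about 20% (12%) |
| 10.7% and 5.3% | 6% | 12% (7%) |

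With 8% v 2% in both subgroups, the likelihood-ratio test rejects in 6% to 7%.

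**The case against.** A reader might go further and infer that the planned analysis cannot answer question 3 at all. The article does not support that.

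- The analysis is labelled explorative in both places, and no power or confirmatory claim rests on it.
- Benefit is not defined as absolute. The aim is to see whether the treatment effect varies, and a logistic interaction is a standard, scale-dependent answer. The plan also uses a log-rank test and time to progression, so the risk difference is one of several effect measures. Subgroup risks and risk differences can be derived from a fitted logistic model.
- The linear regression for severity of disability compares mean benefits additively and does not depend on event counts.
- An infinite estimate does not disable the test: the likelihood-ratio version stays near its nominal level.
- The gain from changing scale depends on how strongly the indicator predicts risk. It is large at a sevenfold contrast in control risk and nearly gone at twofold once the small-sample correction is used.
- Empty cells are a problem of categorical indicators. The composite event includes surgery in the conservative arm and all-cause death, so it may exceed 8%.

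All of this stands and limits the point. It does not remove it. The article names the logistic interaction as the method for success rate, so this is not merely something left to an analysis plan that is not shown. The scale mismatch with the plan's own difference in success rates does not go away with more events. Nor does the article say that a non-significant interaction will be read as equal benefit; the risk is that nothing else is named to set against it.

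**Conclusion.** The point holds in a limited form. For success rate, the one named method tests equality of odds ratios. Under the planned odds ratio, that is compatible with absolute benefits from about 3 to 12 points across control risks of 4% to 16%. At the planned 8% v 2%, a two-level indicator gives no finite maximum-likelihood interaction odds ratio in about 49% to 70% of trials with 125 per arm, and 61% to 78% with 100.

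These figures assume 1:1 allocation, a two-level indicator with a 50/50 to 20/80 split, and equal risks across subgroups for the zero-cell calculation. They fall quickly if events are more frequent: at 16% v 4% with 125 per arm the range is 15% to 38%. If 8% and 2% were meant as annual rates with 20% annual loss, which the text does not say, about 30 events would be expected. That is close to the 20% v 5% row, and the sparse-cell problem would largely vanish for balanced indicators. The scale point does not depend on the number of events.

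This is a worthwhile improvement to an exploratory analysis. It is not a flaw that invalidates it.

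**What to change.** In the statistical analysis section, for question 3 and the success rate:

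1. Keep the logistic interaction, but fit it with a penalised (Firth) or exact method so that empty cells still give a usable result.
2. For each indicator (for example AADI 5–8 v 8–12 mm), add the event risk per arm, the 5-year risk difference in each subgroup and the difference between these, with 95% confidence intervals suited to small cells.
3. State that a non-significant odds-ratio interaction is not evidence of equal benefit.

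The linear regression for disability needs no change. The cost is a few sentences and a little more analysis, with no new data or patients. The downside is wide intervals (half-width about 11 to 12 points for the difference between subgroup risk differences). The additions put the result on the scale of the main comparison and make it estimable, but they do not add information, so it stays exploratory.
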